### Recruitment

At adolescents’ admission to the residential institutions taking part in the study, the CRIES-13 is included in the standard questionnaire battery that adolescents fill out at intake. Adolescents with a clinical score of posttraumatic symptoms on the CRIES-13 (≥30), filled in less than 3 months before T1, will be considered eligible participants for this study. We will include adolescents with clinical levels of posttraumatic symptoms rather than adolescents who qualify for the diagnosis of posttraumatic stress disorder because many adolescents who do not meet the criteria for posttraumatic stress disorder do suffer from posttraumatic symptoms and are in need of treatment [50].

Additionally, clinicians will be asked whether the adolescent in question can be invited to take part in this study. After clinician consult, eligible participants will be contacted by the coordinating researcher who will explain the studies. We will obtain verbal and written assent from all participants, and when they are younger than the age of 16, also written consent from their legal guardians. Potential participants will be invited for an individual meeting with the coordinating researcher who will explain the study. Participants will be explicitly informed about the study design and that they can quit study participation at any moment without disadvantages. The researcher will also bring information letters with information on all aspects of the study. When adolescents initially agree to participate, they will be given the information letters, and 2 to 3 weeks later, they will be asked for their written assent and invited for the pretest measurement (T1).

### Allocation and Randomization

If all inclusion and no exclusion criteria are fulfilled, participants will be randomly assigned (1:1 ratio) to 1 of the 2 groups using a randomization schedule that is generated by a Python script and stratified by gender, intellect, and residential institution. Allocation to groups is not masked, but participants and their mentors will not be informed about the specific expectations regarding posttraumatic symptoms and neurobiological stress reactivity. We will explain that Muse is a relaxation app, designed to help participants deal with stress. Participant enrollment and assignment to the groups will be performed by the first author.

### Interventions

All participants receive treatment as usual: the treatment as recommended by their clinicians regardless of this study (eg, individual or family therapy; medication). There are no restrictions for the type of interventions that participants can receive other than trauma-focused treatment, we only keep track of them. Participants in the intervention group will receive the intervention sessions as an addition to treatment as usual.

Muse is a game-based meditation app that is played on an iPad with a electroencephalography (EEG)–based headband that utilizes real-time neurofeedback. The intervention takes 6 weeks and consists of two 15- to 20-minute gameplay sessions per week. If participants are unable to make it to a session, this session will be rescheduled. All participants will complete 12 gameplay sessions in total. These sessions will take place in an office room located on the campus of the residential institution. Muse includes 10 relaxation tutorials that resemble elements of trauma-focused cognitive behavioral therapy such as deep-breathing techniques [42]. The tutorials are followed by 3-minute meditation sessions. The meditation tutorials are in English, so we have created a standardized protocol with Dutch translations of each tutorial. The gameplay sessions will be supervised by research assistants who are trained to explain the tutorials according to this protocol.

Participants can choose the in-game environment that will be shown during the meditation sessions (eg, beach, rainforest, city park). Before each tutorial, a short calibration will take place, during which the headband records the participants’ brain activity during rest, as a reference point for the upcoming meditation session. The tutorials are followed by 3-minute meditation sessions. Participants will complete at least 2 tutorials and subsequent meditation sessions each intervention session. During the meditation sessions, participants hear sounds in the in-game environment that they have chosen. The EEG-based headband provides real-time neurofeedback that is reflected by the intensity of activity in the environment. When the participant's mind is calm, the environment shows calm and settled winds, but these winds will pick up and blow when the participant's mind becomes more active. When participants succeed in remaining in a calm state for a sufficient amount of time, they will hear birds whistling. The neurofeedback element of the intervention involves retraining brain patterns through operant conditioning. Neurofeedback reinforces individuals’ relaxation abilities [51] and can reduce posttraumatic symptoms [52].

After each meditation session, participants get feedback on their performance through a series of simple graphs. In order to motivate, Muse calculates points, provides awards, and sets goals and challenges. Performances are saved and tracked so participants can see their progress over time.

^h^HPA: hypothalamic-pituitary-adrenal.

Participants will watch an aquatic video for 5 minutes [53] to derive basal autonomic nervous system parameters during rest, in order to compare to the autonomic nervous system parameters derived during the stress task. The social stress task is an adapted and combined version of the Trier Social Stress Task for Children (TRIER-C) [54,55] and the Sing-a-Song Stress Test (SSST) [56]. Participants receive the introduction of a story and are told that they have 5 minutes to compose the end of the story. Then, they will present their story for 4 minutes in front of a camera. Unlike the original TRIER-C, the judge panel will be replaced by a video camera [57]. Participants will be recorded, allegedly for later assessment by a group of peers who will judge their performance. If the participant does not complete the 4 minutes for presenting, the researcher can use a standard set of prompts to encourage further narration. Immediately after the 4 minutes, participants will be asked to fill in a 3-item manipulation check to rate how nervous the presentation task has made them on a scale from 1 (not nervous at all) to 10 (very nervous). Next, participants are given a booklet with song texts and are told that they have to sing a song in front of the camera. Participants have 30 seconds to choose a song and are expected to sing the song aloud for 30 seconds. Again, they will be asked to fill out the manipulation check immediately after the task. For an overview of the stress task, see Table 2. Participants will not be fully debriefed until they completed the second stress task at T2.

**Table 2 table2:** Overview of the social stress task to measure neurobiological reactivity to acute stress.

Task timeline			Activity		ANS^a^ recordings		Cortisol samples
**Before**							
	–20 minutes	—		—		–20	
	–5 minutes	Aquatic video		Basal ANS parameters		—	
	0 minutes	—		—		Pre	
**Start**							
		Anticipation speech task		ANS reactivity		—	
		Speech task		ANS reactivity		—	
		Manipulation check		—		—	
		Anticipation song task		ANS reactivity		—	
		Song task		ANS reactivity		—	
		Manipulation check		—		—	
**After**							
	0 minutes	Recovery		ANS recovery		Post	
	10 minutes	—		—		+10	
	20 minutes	—		—		+20	
	40 minutes	—		—		+40	

^a^ANS: autonomic nervous system.

The posttest (T2) will take place in week 8 and includes, like the pretest (T1), an interview, aquatic video, social stress task, and a hair cortisol measurement. Since participants will be exposed to the social stress task twice, it is expected that they show habituation-related decreased levels of stress at T2 [58,59]. To lower the risk for stress habituation and to improve methodological rigor for the second social stress task, participants will be given another story introduction that is comparable to the story that will be used for T1. At the end of T2, participants will be debriefed and told that the video recordings were deleted immediately after the measurement session.

The 2-month follow-up will take place in week 16 and includes an interview, aquatic video, and a hair cortisol measurement. The 2-month follow-up measurement is conducted to provide additional information about potential long-term intervention effects. Therefore, we will use questionnaires and the parameters to measure neurobiological activity during rest that are relatively simple to obtain (ie, a 5-minute autonomic nervous system measurement during the aquatic video and cutting the hair). Measuring neurobiological reactivity requires the execution of a stress task that is time-consuming, and even more important, eliciting stress among traumatized adolescents is not without risks and should only be done when essential for research purposes. For those reasons, neurobiological reactivity to acute stress was not included at 2-month follow-up measurement.

Participants will receive a gift voucher of €15 (approximately US $17.86) at T1, a gift voucher of €10 (approximately US $11.91) and a stress ball at T2, and a gift voucher of €15 at 2-month follow-up measurement. Participants’ mentors (ie, the group home worker with whom they have the most contact) will fill in the questionnaires in the same week as when the measurements with the participants are conducted.

### Measures

#### Questionnaires

The screening instrument is the CRIES-13 [49], a questionnaire with 13 four-point items to screen whether adolescents suffer from posttraumatic symptoms.

Posttraumatic symptoms will be measured by participants’ self-report as well as by mentor report. The Child Report of Posttraumatic Symptoms (CROPS) [60] is a self-report questionnaire that consists of 24 three-point items. The Parent Report of Posttraumatic Symptoms (PROPS) [60] is a 30-item questionnaire that measures posttraumatic symptoms as reported by parents or other caretakers. In this study, participants’ group home mentors will fill out the questionnaire. Several studies have demonstrated the validity and reliability of the CROPS and the PROPS in general populations [61]. Additionally, the CROPS has been validated in a sample of juvenile offenders [62]. The CROPS and the PROPS have been jointly developed so that the CROPS focuses on internal thoughts and feelings, whereas the PROPS focuses on observable behaviors.

Stress will be examined with the 7-item stress subscale of the Depression Anxiety Stress Scales (DASS-21) [63,64]. The DASS-21 is a self-report questionnaire that in total consists of 21 four-point items. Its validity and reliability are good and the subscales have an excellent internal consistency [63].

Anxiety will be measured with the 7-item anxiety subscale of the DASS-21 [63,64].

Depression will be measured with the 7-item depression subscale of the DASS-21 [63,64].

Aggression will be measured by participants self-report as well as by mentor report. The Reactive and Proactive Aggression Questionnaire (RPQ) [65] is a self-report questionnaire that is composed of 23 three-point items. The RPQ consists of proactive aggression and reactive aggression subscales. Its validity and reliability are good, and both subscales have good internal consistency [65]. The Parent-rating scale for Reactive and Proactive Aggression (PRPA) [66] is a questionnaire that can be filled out by parents or other caretakers. The PRPA has 11 three-point items and consists of reactive aggression and proactive aggression subscales. The PRPA total score and both its subscale scores have good validity [66].

#### Neurobiological Activity During Rest

Autonomic nervous system parameters will be measured with the *Vrije Universiteit* Ambulatory Monitoring System (VU-AMS) [67,68]. This a lightweight ambulatory device that records electrocardiograms and changes in thorax impedance with 5 electrodes that are placed on participants’ chest and 2 that are placed on the back. The electrocardiogram has a sampling rate of 1000 Hz and heart rate is obtained from the time between 2 adjacent R peaks. Heart rate data will be extracted and visually inspected for artifacts with the *Vrije Universiteit* Data Analysis and Management Software program (VU-DAMS; version 4.0) [69]. We will derive heart rate, respiratory sinus arrhythmia, pre-ejection period, respiration rate, and skin conductance parameters from the VU-AMS recordings.

Basal autonomic nervous system parameters during rest will be derived from VU-AMS recordings while participants are watching an aquatic video for 5 minutes [53].

For basal hypothalamic-pituitary-adrenal axis activity, basal cortisol levels will be measured in participants’ hair. Whereas saliva captures real-time cortisol levels that are subject to major fluctuations [70], hair cortisol provide a reliable way to assess average long-term activity of the hypothalamic-pituitary-adrenal axis (thus cortisol exposure over longer time). Hair samples will be cut as close to the scalp as possible from a posterior vertex position. At least 15 mg of the most proximal 1.5 cm of each hair sample will be used for analysis—representing the basal level over the 6 weeks before the hair sample was taken. Hair processing and analyses will be conducted by the Laboratory of Endocrinology of the Erasmus Medical Center, Rotterdam, the Netherlands. Hair samples will be washed in isopropanol and after solid phase extraction, hair cortisol will be quantified by liquid chromatography–tandem mass spectrometry [71].

#### Neurobiological Reactivity to Acute Stress

For autonomic nervous system reactivity to acute stress, autonomic nervous system parameters will be measured while participants complete the social stress task (see Table 2). We will derive autonomic nervous system parameters during the following segments of the stress task: (1) anticipation speech task, (2) performing speech task, (3) anticipation song task, (4) song task, and (5) recovery.

For hypothalamic-pituitary-adrenal axis reactivity to acute stress, salivary cortisol levels will be measures before and after completion of the social stress task (see Table 2). Six saliva samples will be obtained with a collection device (Salivette; Sarstedt AG and Co) twenty minutes (–20), immediately before the social stress task (pre), immediately after (post), ten minutes (+10), twenty minutes (+20), and forty (+40) minutes after the task (Table 2). Cortisol levels will be measured using the liquid chromatography–tandem mass spectrometry method with CHS MSMS Steroid kit (PerkinElmer).

### Sample Size Calculation

Power calculations were performed using G*Power [72]. An a priori power analysis for analysis of variance (repeated measures, within-between interaction) was conducted. Based on previous meditation-based interventions for posttraumatic stress [32,34-36,73], we expected a small to medium effect size of *d*=0.30 and a repeated measures correlation of 0.60. To achieve a statistical power of at least .80, a sample size of 72 participants was required. We aim to include 80 participants in total to allow for 10% attrition, which was estimated from previous studies [44,45,47] on game-based interventions in this population.

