**Methods:**

This will be a multicenter, multi-informant, and multimethod randomized controlled trial. Participants will be adolescents (N=80), aged 10 to 18 years, with clinical levels of posttraumatic symptoms, who are randomized to receive either the Muse therapy sessions and treatment as usual (intervention) or treatment as usual alone (control). Data will be collected at 3 measurement instances: pretest (T1), posttest (T2), and at 2-month follow-up. Primary outcomes will be posttraumatic symptoms (self-report and mentor report) and stress (self-report) at posttest. Secondary outcomes will be neurobiological stress parameters under both resting and acute stress conditions, and anxiety, depression, and aggression at posttest. Secondary outcomes also include all measures at 2-month follow-up: posttraumatic symptoms, stress, anxiety, depression aggression, and neurobiological resting parameters.

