## Methods

### Study Design

This study is a multicenter randomized controlled trial with 2 parallel intervention groups. Outcomes will be compared at 3 measurement instances: before the intervention (T1), immediately after the intervention (T2), and at a 2-month follow-up. Participants will be randomly assigned to the intervention or the treatment-as-usual (control) group, stratified by gender and intellect to ensure equal ratios of participants in both groups.

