### Statistical Analysis

To assess intervention efficacy, we will use repeated measure analysis of variance to detect differences in mean outcome scores between the 2 groups at T2 and at 2-month follow-up. All analyses will be conducted in accordance with the intention-to-treat principle. Missing data will be imputed using Markov Chain Monte Carlo [74]. Results will be expressed as differences in mean scores between the 2 groups with 95% confidence intervals. *P* values<.05 will be considered statistically significant.

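### The 72 participants give 80% power for a 0.60 SD between-group difference in change, not for the stated d=0.30, at which power is about 29%

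*Protocol article*

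**What the plan says.** The Sample Size Calculation section names the procedure: "An a priori power analysis for analysis of variance (repeated measures, within-between interaction) was conducted". Its inputs are given as "we expected a small to medium effect size of *d*=0.30 and a repeated measures correlation of 0.60", and its result as "To achieve a statistical power of at least .80, a sample size of 72 participants was required". The number is then raised to 80 for 10% attrition. The section does not print the f entered, the number of measurements or any nonsphericity correction, and it does not say what d is a difference between or what SD it is divided by.

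Other sections supply the rest:

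- Significance level (Statistical Analysis): P "values<.05 will be considered statistically significant".
- Allocation (Allocation and Randomization): "participants will be randomly assigned (1:1 ratio) to 1 of the 2 groups".
- Primary endpoint (Abstract, Methods): "Primary outcomes will be posttraumatic symptoms (self-report and mentor report) and stress (self-report) at posttest".
- Target (Objectives): a larger fall in symptoms and stress with Muse added to usual treatment than with usual treatment alone.
- Reporting (Statistical Analysis): differences in mean scores between the groups, with 95% confidence intervals.

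**The concern.** The d of a two-group comparison and the f of a repeated-measures interaction are on different scales. The conversion f = d/2 holds for two independent means compared once. In G*Power's within-between interaction test, f is the SD of the interaction residuals of the group-by-time cells, divided by the outcome SD. A difference in change between two groups is spread over four cells there, so the same f stands for twice as large a difference. If d/2 was entered, the trial was sized for an effect of 0.60 SD and described as sized for 0.30 SD.

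The power statement is what a reader will use to interpret a null result. Taken at face value, it makes a non-significant result look like fair evidence against a small to medium benefit. If the true power at that effect is near 30%, the trial would miss such a benefit about 70% of the time.

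**Working it through.** **Inputs.** From Sample Size Calculation: within-between interaction, d = 0.30, correlation ρ = 0.60, power .80, N = 72. From Statistical Analysis: α = .05. From Allocation and Randomization: k = 2 groups, 1:1. Inferred: m = 2 measurements (pretest and posttest, matching the primary endpoint) and f = d/2 = 0.15.

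**1. Reproducing 72.** G*Power's default for this test is a noncentral F with

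λ = f² N m / (1 − ρ), df1 = (k − 1)(m − 1), df2 = (N − k)(m − 1).

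With f = 0.15, m = 2, N = 72: λ = 0.0225 × 72 × 2 / 0.40 = 8.10, df = 1 and 70, power 0.8015. At N = 70, λ = 7.875 and power is 0.790. So 72 is the smallest even N that reaches .80.

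Other entries at ρ = 0.60 and power .80:

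| Entry | N |
|---|---|
| f = 0.15, m = 3 | 60 |
| f = 0.15, m = 3, nonsphericity ε = 0.75 | 72 |
| f = 0.30, m = 2 | 20 |
| f = 0.30, m = 3 | 16 |
| f = 0.15, m = 2, α = .10 | 58 |
| f = 0.15, α = .05/3, m = 2 or 3 | 96 or 78 |
| SPSS-type effect size, f = 0.15, m = 2 or 3 | 354 or 218 |
| SPSS-type effect size, f = 0.30, m = 2 or 3 | 92 or 58 |
| Cohen-type effect size, f = 0.15, m = 2 or 3 | 352 or 430 |
| Cohen-type effect size, f = 0.30, m = 2 or 3 | 90 or 110 |

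Both routes found to 72 use f = 0.15.

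**2. What f = 0.15 means.** In a 2 × 2 interaction the cell residuals, in SD units, are +f and −f in alternating cells. The difference in change is

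Δ = [f − (−f)] − [(−f) − f] = 4f = 4 × 0.15 = 0.60 SD.

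As a check, with m = 2 the interaction F test is the t test on change scores. The change-score variance is 2(1 − ρ)σ², so its noncentrality is NΔ² / [8(1 − ρ)]. Setting this equal to 2Nf² / (1 − ρ) gives Δ² = 16f², hence Δ = 4f. A difference of 0.30 SD corresponds to f = 0.075.

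**3. Power at 0.30 SD.** SD of change = √(2 × 0.40) = √0.80 = 0.894 SD. Standardised effect = 0.30 / 0.894 = 0.335. With 36 per arm the noncentrality is 0.335 × √(36/2) = 1.42, against a two-sided critical value of 1.994 on 70 df: power 0.289. With 40 per arm it is 0.316. At Δ = 0.60 SD and 36 per arm it is 0.8015, the plan's own figure.

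**4. Other readings of d = 0.30.**

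| Reading or analysis | N = 72 | N = 80 |
|---|---|---|
| Difference in change, outcome SD units (planned interaction test) | 0.289 | 0.316 |
| Standardised by SD of change, or posttest scores alone | 0.241 | 0.263 |
| Baseline ANCOVA, residual variance 1 − 0.60² = 0.64 | 0.348 | 0.381 |
| One-sided test on change | 0.407 | 0.437 |
| Three time points, 0.30 SD at both posttest and follow-up | 0.287 | not run |

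**5. Size needed for 80% power at 0.30 SD.** 282 with the interaction test (282 / 0.90 ≈ 314 with 10% attrition), or 226 before attrition with ANCOVA.

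**6. Expected precision at N = 72.** Half-width of the 95% interval for the difference in change: 1.994 × 0.894 × √(2/36) = 0.42 SD. With ANCOVA: 1.994 × 0.80 × √(2/36) = 0.38 SD. Both exceed 0.30.

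**7. Attrition step.** 72 / 0.90 = 80, which is correct.

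**The case against.** The strongest reply is that the G*Power settings are not in the article. Both f = 0.15 and m = 2 are inferred, and three measurements with ε = 0.75 also give 72, so two measurements are not established. This stands, and the settings should be described as inferred. It does not save the power claim. The second route also uses f = 0.15, which there corresponds to about 0.64 SD if the same difference holds at posttest and follow-up. The 0.60 SD and 29% figures for the pretest-to-posttest contrast follow from N = 72 and ρ = 0.60 alone.

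A second reply is that d is undefined. If the authors meant d = 2f on the software's own scale, the number is internally consistent and the fault is an unexplained metric. That is true in form. But d would then be half the between-group difference in change. The article does not say so, and its Objectives and Statistical Analysis sections speak of between-group contrasts.

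Third, the planned analysis is repeated-measures ANOVA, so ANCOVA power does not belong in the main statement. This is fair, and those figures are context only. Fourth, the article already promises 95% confidence intervals and nowhere says it will read a null result as evidence against d = 0.30. That lessens the harm but leaves the printed power figure wrong.

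**Conclusion.** The concern holds. The stated power of at least .80 does not go with a between-group effect of d = 0.30. With 72 participants, ρ = 0.60 and two-sided α = .05, the trial has 80% power for a difference in change of 0.60 SD and 29% for 0.30 SD. Retaining all 80 participants raises the latter to 32%.

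The conclusion assumes that d is a between-group difference in pretest-to-posttest change (or at posttest, with equal baselines) in units of the outcome SD. Standardising by the SD of change lowers power to 24%, and baseline adjustment raises it to 35%. None of the two-sided readings tried exceeds 38%, even with 80 participants. For 0.30 SD to have 80% power at N = 72, the correlation would have to be about 0.90 instead of the stated 0.60. How f was entered is an inference, but the shortfall does not depend on it.

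**What to change.** Keep the target of 80 and rewrite the sample size paragraph so that it:

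- defines d (which contrast, which SD) and prints the f, number of measurements, nonsphericity setting and alpha that were entered;
- says that 72 completers give 80% power for a between-group difference in change of 0.60 SD under the planned repeated-measures ANOVA, and about 29% for 0.30 SD;
- says that a non-significant result does not exclude d = 0.30 and will be interpreted from the 95% confidence interval, whose expected half-width is about 0.42 SD.

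If the authors want to mention baseline ANCOVA (80% power at about 0.54 SD, 35% at 0.30 SD, half-width 0.38 SD), it should be labelled as an alternative to the planned analysis.

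The cost is one reworded paragraph and a less favourable power statement. No extra participants are needed, and no conduct or analysis step changes.
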